### **2.2 Exploratory Objectives**

**2.2.1:** To assess the preliminary effects of a 5-day tDCS treatment protocol on depressive and cognitive symptoms in individuals with TRD.

**Hypothesis 2.2.1a:** We hypothesize that patients treated with the 5-day tDCS treatment protocol will have a decrease in mean Montgomery-Asberg Depression Rating Scale (MADRS) scores post-tDCS.

**Hypothesis 2.2.1b:** We hypothesize that patients treated with the 5-day tDCS treatment protocol will demonstrate changes in cognitive measures (Stroop Test, Revised Hopkins Verbal Learning Test (HVLT-R), and Digital Symbol Coding Test (DSCT)) post-tDCS.

**2.2.2:** To explore EEG changes in peak alpha frequency (PAF) data as a potential biomarker to measure desired brain stimulation effects of tDCS in the stimulated brain region.

**Hypotheses 2.2.2.a:** We hypothesize that the baseline PAF will have an indirect correlation with baseline MADRS scores in depressed patients.

**Hypothesis 2.2.2b:** We hypothesize that there will be an increase in mean PAF scores post-tDCS.

**2.2.3:** To explore cerebral hemodynamic changes as measured by functional near-infrared spectroscopy (fNIRS) as a potential biomarker to measure desired brain stimulation effects of tDCS in the stimulated brain region.

**Hypotheses 2.2.3a:** We hypothesize that there will be an increase in cerebral hemodynamics post-tDCS.

### 3 Study Design

#### 3.1 General Design

In this feasibility study we propose to conduct a 5-day tDCS treatment protocol in hospitalized adult patients with TRD, with each treatment session lasting for 30 minutes, delivered twice daily, for a total of 10 stimulations over 5 days. (Figure 1)

[figure not shown]

Before and after the 5-day tDCS treatment protocol, assessments will include Montgomery-Asberg Depression Rating Scale (MADRS) to measure depressive symptoms, Snaith-Hamilton Pleasure Scale (SHAPS) to measure anhedonia, Stroop Test to measure memory and executive function, Revised Hopkins Verbal Learning Test (HVLT-R) to test verbal learning and memory, and Digital Symbol Coding Test (DSCT) to measure working memory. (Figure 2) EEG for objective electrophysiologic data will also be collected before and after tDCS. A wireless EEG unit (CGX, Cognionic, Inc.) (Section 5)

Figure 2. Study schema

[figure not shown]

will be used to collect EEG and peak alpha frequency (PAF) as potential target engagement marker for tDCS. The PAF measures the highest magnitude within the alpha range of brain oscillations, thought to reflect cognitive performance. Cerebral hemodynamics using fNIRS with the NIRSIT system (OBELAB Inc.) will be measured before and after tDCS. fNIRS indirectly measures cortical oxygenated and deoxygenated hemoglobin levels, providing insights into neural activation before and after brain stimulation. Other potential predictors of treatment response measures collected at baseline include Adverse Childhood Experiences (ACE), premorbid intelligence quotient (pIQ), Wide Range Achievement Reading Test (WRART), and Socioeconomic Status (SES).

### **3.2 Primary Study Endpoints**

The primary goal of this study is feasibility, acceptability, and tolerability of administering a 5-day tDCS treatment protocol in acutely hospitalized TRD patients.

#### **Feasibility**

We define feasibility as 70% of eligible patients choosing to enroll in the study. Other feasibility parameters will include willingness of clinicians to refer and help recruit patients, number of eligible participants, willingness of participants to enroll, retention of patients, and completeness of data collection.

#### **Acceptability**

We define acceptability as 80% of study participants completing 80% of the 10-session tDCS treatment protocol. We will also ask participants about their satisfaction, perceptions, and experiences with the tDCS treatments. Other acceptability parameters will include rates of adherence to tDCS protocol, dropout rates and reasons for non-completion.

#### **Tolerability**

We define tolerability as an overall tolerability rating of "very tolerable." This will be a self-report based on a global question "Considering all aspects of your experience, how would you rate the overall tolerability of the tDCS intervention?" The response options are: very tolerable, somewhat tolerable, neutral, somewhat intolerable, and very intolerable. We will ask this question after the last tDCS session. Other tolerability parameters will include the tDCS adverse effects questionnaire.

### **3.3 Exploratory Study Endpoints**

The exploratory endpoint for this study will be to observe the changes in measures of depressive symptoms based on Montgomery-Asberg Depression Rating Scale (MADRS) and anhedonia based on Snaith-Hamilton Pleasure Scale (SHAPS); cognitive measures including Stroop Test, Revised Hopkins Verbal Learning Test (HVLT-R), and Digital Symbol Coding Test (DSCT). Response is defined by a 50% or more reduction in MADRS score.

An exploratory marker of response to tDCS is EEG peak alpha frequency (PAF) which will be measured pre- and post-tDCS. Another exploratory marker of response to tDCS is cerebral hemodynamic changes pre- and post-tDCS as measured by fNIRS using the NIRSIT system (OBELAB Inc.). Other exploratory predictors of treatment response include Adverse Childhood Experiences (ACE), premorbid intelligence quotient (pIQ), Wide Range Achievement Reading Test (WRART), and Socioeconomic Status (SES). These measures will only need to be administered once at the pre-treatment assessment.

### **3.4 Primary Safety Endpoints**

Monitoring for adverse events will be conducted during study period. Subjects will be asked to complete the tDCS Adverse Effects questionnaire after each tDCS treatment. Overall incidence of all AEs and SAEs, as well as incidence of specific AEs and SAEs, will be determined.

The tDCS adverse effects questionnaire lists 12 possible tDCS side effects and asks a participant to rate whether they experienced any on a 4-point Likert scale (ranging from 1 - absent to 4 - severe), and to what extent they attribute each side effect to tDCS (ranging from 1 - not at all to 4 - completely).[11]

## **4 Subject Selection, Enrollment and Withdrawal**

Adult patients hospitalized in Generose will be eligible for the study.

### **4.1 Inclusion Criteria**

- 18 years and older
- Clinical diagnosis of treatment-resistant depression (defined as depression that does not remit following two or more treatment attempts of an adequate dose and duration of a minimum duration of 4 weeks)
- Hospitalized in Generose Psychiatric Units
- Voluntary admission status
- Moderate or severe depression, defined by PHQ-9  $\geq 15$
- Ability to provide informed consent
- Ability to adhere to protocol

### **4.2 Exclusion Criteria**

- Bipolar disorder
- Active primary psychotic or substance use disorders (except nicotine dependence) within the past year
- Any active neurological condition (including seizure disorder, traumatic brain injury, stroke)
- Contraindications to tDCS (including pacemaker, metallic implants in the head or neck [except orthodontic hardware], skin disease causing irritation)
- Current pregnancy or positive urine pregnancy test (clinical)
- Any neuromodulation therapy (including ECT, rTMS, DBS, VNS, TES) within the last 3 months

### **4.3 Subject Recruitment, Enrollment and Screening**

To ensure representativeness of an inpatient population, potential subjects will be recruited from both GE3W (Mood Disorders Unit where patients typically have TRD) and GE3E (Medical Psychiatric and Geriatric Psychiatric Unit where patients either have medical-psychiatric conditions or are older adults 65 years and older) inpatient units. Other than age requirement of 18 years or older and ability to provide informed consent, patients who meet inclusion criteria and are willing to participate will be enrolled regardless of sex and gender, race, or ethnic group and social determinants.

Study coordinators will review Epic for daily admissions to the inpatient units to pre-screen for eligibility. When a potential subject is identified, the study coordinators will review with the PI or Co-Investigator for appropriateness, and then ask permission from the primary inpatient treatment team consultant or providers to approach the patient. With the primary service's permission, the study coordinator will explain the study to the patient, answer questions about the study, and enroll and obtain written informed consent from the patient.

### **4.4 Early Withdrawal of Subjects**

#### **4.4.1 When and How to Withdraw Subjects**

Subjects will be withdrawn from the study prior to completing study procedures in the following circumstances:

- Subject decision to withdraw from the study (withdrawal of consent)
- Subject inability to adhere to protocol requirements
- Severe adverse effects (SAEs) requiring medical intervention
- If the investigators determine it is in the best interest of the subject

There are no anticipated risks particular to early or abrupt discontinuation of tDCS. If subjects discontinue tDCS treatments or withdraw early and require ongoing medical treatment, appropriate referrals will be arranged. Should a subject experience any medical emergency during participation in a study visit, whether related to the study or not, the subject will be evaluated by clinical on-call inpatient psychiatric staff.

If an enrolled subject withdraws from the study prior to completion, an attempt will be made to enroll another subject in order to achieve the target enrollment.

#### **4.4.2 Data Collection and Follow-up for Withdrawn Subjects**

Data collected from subjects who withdraw from the study (whether due to subject withdrawal or withdrawal by the investigators) prior to the time of withdrawal will be included in data analyses. Subjects who discontinue tDCS treatments will be invited to continue participation in the post-tDCS assessments and this data will be collected with informed consent.

## 5 Study Device

### 5.1 Description

#### tDCS device

The Soterix Medical 1×1 Low Intensity Transcranial DC Stimulator Model 1300A is an investigational device manufactured by Soterix Medical, Inc. (New York, NY, USA). It is designed for use in noninvasive transcranial stimulation of the brain by delivering low-intensity electrical current to the scalp through two electrodes. (Figure 3)

The stimulator is comprised of a small control box (length: 7.91 in., width: 5.9 in., height: 2.83 in.) that contains the power source (two 9-volt alkaline batteries), displays (actual current delivered, impedance/contact quality, stimulation time remaining, low battery indicator), and controls (power, current intensity, stimulation duration, stimulation “start”, and emergency abort). The device’s maximum output voltage is  $40\text{ V} \pm 5\%$ , and maximum output current is  $2000\text{ }\mu\text{A}$  (2 mA) DC  $\pm 1\%$ .

Figure 3. tDCS and electrode placement

Figure 4. Electrode cables connected to tDCS stimulator

The stimulator is connected to each electrode (an anode and a cathode) by a color-coded, rubber-coated cable. (Figure 4) The conductive rubber electrode inset pads are covered by  $5 \times 7\text{ cm}$  ( $35\text{ cm}^2$ ) sponges that are held against the scalp by a pair of adjustable, hypoallergenic/latex-free elastic bands (3 cm wide) or rubberized head straps. The sponge covers are soaked in normal saline (0.9% NaCl) prior to stimulation. The electrode insets, electrode cables, sponge covers, and elastic bands/head straps are supplied with the device by the manufacturer.

#### Wireless EEG device

EEG is the measurement, through the use of sensors and amplifiers, of scalp surface electrical potentials arising from cortical activity. The Quick-20r is a wireless, battery-operated EEG headset utilizing dry sensor technology. It allows the international 10-20 system standard channel positions/electrode placement across the scalp.

The 10-20 system derives its name from measurements of 10% and 20% of the distance between landmarks on the head, specifically, the depression above the bridge of the nose (nasion), the bump at the back of the head (inion), and the depressions in front of each ear (preauricular points). Sensors are labeled with a combination of letters and numbers indicating their respective locations, with even numbers on the right and odd numbers on the left side of the head. Midline locations are marked with a “z” for “zero.” For instance, Fz sits on the frontal midline, while F3 sits left of and F4 sits right of Fz.

The headset provides an integrated approach to the wireless acquisition of recorded EEG signals. (Figure 5) Wireless technology allows the subject to move about while real-time data is collected and displayed. The headset obtains high-quality EEG with minimal scalp preparation. Patented mechanisms and replaceable dry sensors align to various head shapes and sizes, maintaining sensor positions in a standard montage. EEG channels are sampled at a time resolution of 500Hz and converted to digital data at 24 bits of resolution. The Quick-20r provides research-grade signal quality and is ideally suited for general-purpose EEG and ERP research in laboratory and field environments.

Figure 5. CGX wireless EEG

## **NIRSIT**

The NIRSIT device is a portable functional near-infrared spectroscopy (fNIRS) device used in this study to transcutaneously measure changes in oxyhemoglobin in the prefrontal cortex using light detection. It is designed to measure variations in cerebral hemodynamics on a realtime basis by radiating a near light beam, at two wavelengths of 780nm and 850nm of laser, into the cerebral cortex. The system comes with its dedicated monitoring and analysis software. (Figure 6)

Figure 6. NIRSIT device system

During the study, the subject wears the NIRSIT, and the researcher runs the software on the tablet screen to measure changes in the subject's oxyhemoglobin. After wearing the NIRSIT, changes in oxyhemoglobin are measured using near-infrared spectroscopy during the word fluency test.

## **5.2 Method for Assigning Subjects to Treatment Groups**

As this is an open-label, pilot trial, no randomization or assignment to different treatment groups will occur. All subjects will receive an identical course of ten 30-minute tDCS treatments at 2 mA over the course of 5 days.

### 5.3 Preparation and Administration of Investigational Device

#### tDCS Preparation

- The subject will be greeted and seated comfortably.
- Details of the subject's session will be recorded in the study file.
- Subjects will be instructed to turn off all cell phones and pagers. Eyeglasses will be removed. Subjects will be instructed to remove any metal objects above the neckline (with the exception of orthodontic hardware), particularly hairpins or large metallic earrings. Subjects will be instructed to sit quietly with their eyes open throughout the procedures.
- The left dorsolateral prefrontal cortex (L-DLPFC) position will be established in relation to external cephalic landmarks. Using a tape measure, the shortest midline distance over the scalp from the subject's nasion to the inion will be measured. The midpoint of this line will be marked on the scalp with a felt-tipped marker or grease pencil. A second line will be measured between the subject's left and right preauricular points (overlying the temporomandibular joints), passing through the midpoint of the nasion-inion line. The intersection of the nasion-inion line and the left-right preauricular line will be defined as the vertex. From the vertex, a point 5 cm lateral to the nasion-inion line (to the subject's left) and 5 cm anterior to the preauricular line will be marked with the marker/pencil. This will be the L-DLPFC reference point.
- The skin surrounding the L-DLPFC point on the subject's scalp and the right supraorbital area on the right forehead will be visually inspected. If free of visible skin injury, the skin will be cleaned with isopropyl alcohol wipes and allowed to dry.
- The stimulator's power switch will be turned to "ON".
- The electrode cables will be connected to the stimulator, with the red cable connected to the red receiver (labeled "ANODE") and the black cable connected to the black receiver (labeled "CATHODE").
- The conductive rubber electrode insets will be inspected visually for any defects and replaced if necessary. One electrode inset will be connected to the anode cable, and one electrode inset will be connected to the cathode cable.
- Two electrode sponge covers will be soaked in normal saline (0.9% NaCl), using approximately 12 mL of saline per sponge. Sponges are to be saturated but not dripping; if dripping they will be squeezed gently until no longer dripping saline.
- The electrode insets, connected to the electrode cables, will be slid into the sponges until the rubber inset is no longer protruding from the sponge.
- The electrodes (conductive rubber electrode inset enclosed by the saline-soaked sponge cover) will be placed on the scalp, with the anode (connected to the stimulator by the red cable) centered on the marked L-DLPFC reference point and the cathode (connected to the stimulator by the black cable) over the right supraorbital area. The operator will ensure that the two sponge covers are at least 5 cm apart in order to avoid forming a short circuit (electrical shunt) along the scalp.
- The electrodes will be held in place by the elastic bands or head straps. Latex-free bands will be used for patients with latex allergies.

#### tDCS Operation

- The operator will verify good contact of the electrodes with the skin using the stimulator's "CONTACT QUALITY" meter. If contact quality is inadequate (less than 50% of maximum contact quality), the operator will adjust electrodes, add a small amount of saline to the electrode sponge covers with a syringe, and/or clean the skin with alcohol wipes again until good contact is established.
- Current intensity will be set at 1 mA using the stimulator's "CURRENT INTENSITY" knob.
- Stimulation duration will be set at 30 minutes using the stimulator's "DURATION" knob.
- The sham control switch (used for sham-controlled trials, not applicable to this study) will be set in the "OFF" position.
- The "RELAX" sliding switch will be set to "FULL CURRENT" (i.e., the full amount set with the "CURRENT INTENSITY" knob in earlier step).
- The operator will give a "preview" of the stimulation sensation by pressing the "PRE-STIM TICKLE" button, which delivers 1 mA of current for 30 seconds prior to the main treatment stimulation. This is intended to provide reassurance for the subject and to ensure initial tolerability. This will be performed only during the first treatment visit.
- To begin the treatment stimulation, the operator will press the "START" button. This will commence a 30-second period during which the stimulator automatically and gradually escalates the current to the full intensity (2 mA), followed by full-intensity DC stimulation for the set duration (30 minutes), and concluding with a 30-second period during which the stimulator automatically decreases current intensity to zero.
- During the treatment session, the subject will be asked to remain seated, relaxed and with eyes open, and to refrain from major voluntary motor activity and conversation (unless communicating with the operator about any discomfort).
- The operator will monitor the subject and the stimulator's actual current and contact quality displays throughout the treatment session.
- If the subject experiences significant discomfort but wishes to proceed with stimulation, the operator can reduce current intensity by sliding the "RELAX" switch to a lower setting. If the subject cannot tolerate the current at full intensity, the operator will attempt to reduce current by 0.2 mA increments (as shown on the stimulator's actual current display) until tolerated.
- Should the stimulation need to be discontinued immediately for any reason, the operator will press the "ABORT" button.
- Following the conclusion of the stimulation session, the electrode assemblies and head straps will be removed from the subject, the stimulator's power will be turned off, and the electrode components and cables will be disconnected. Cables and rubber electrode insets will be cleaned with alcohol wipes between sessions.
- The operator will inspect visually the subject's skin under the electrodes to determine if there is any indication of injury.

### **EEG placement on the subject's head**

- Grasp each handle and gently pull them apart to open the headset.
- Slide the headset over the subject's head.

- Adjust the position of the headset so the earpads fit around the subject's ears .
- Brush aside excess hair near and underneath the earpads.
- Position Fp1 and Fp2 to sit 1cm above the eyebrows.
- Reorient misaligned legs and pods.
- Grasp and rotate each pod so the sensor is perpendicular to the subject's head.
- Push the headset downward so the sensor at the crown (Cz) makes firm contact with the subject's head.
- Ensure pods lie flat on the subject's head.
- Brush aside excess hair on the forehead and any other positions where Drypad sensors are installed.
- Lift the earpad to access the ear lobe and clean with alcohol.
- Clip the A1 earclip to the left earlobe.
- Option: Attach the A2 earclip to the right earlobe.
- Option: Attach ExG passive lead wire on the A2 handle for additional biometric measurements.
- Verify headset is properly positioned on the subject's head.

### **EEG recording**

- After properly positioning the headset, obtain direct contract on all sensors before recording
- Use LEDs to assist in making contact with the scalp on each position and check the impedance measures on each channel. Green color indicates acceptable impedance within range ( $< 2500 \text{ k}\Omega$ )
- Click record in the software on the dedicated laptop or iPad device after reaching acceptable impedance level on all channels.
- The software will prompt the user for a file name and filetype.
  - Enter the following for the filename:  
tDCS\_[subject number]\_[pre OR post]
  - Select .eeg as filetype. (This option is only available if the laptop is used)
- Close out the current file in the software and exit program followed by pressing power button to turn off the device

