## **1.4 Study Rationale and Risk Analysis (Risks to Benefits Ratio)**

### **1.4.1 Study Rationale**

Some tDCS studies included TRD populations, but no studies have been conducted in inpatient settings. Patients hospitalized psychiatrically for TRD have high severity of symptoms, more failed prior treatments, and are at high risk for suicide and disability. Most of these patients feel they have tried enough medications and want to try a non-medication treatment approach. Hospitalization provides a window of opportunity to test whether adding tDCS as an adjunctive treatment to standard inpatient psychiatric care for TRD could be a viable option. In addition to offering patients a novel treatment and more hope for getting better, it could potentially decrease hospital length of stay.

We therefore propose to test the feasibility, acceptability and tolerability of using tDCS in the inpatient setting with TRD patients, explore the utility of EEG biomarkers to assess response to tDCS, and assess preliminary impact on depressive and cognitive symptoms. This proposed pilot project will leverage existing equipment and resources within the Depression Center, which includes a Soterix tDCS platform and a CGX wireless EEG system that will be used to generate a peak alpha frequency (PAF) as a potential biomarker to assess response to tDCS.

For our study purposes, we define TRD as "depression that does not remit following two or more treatment attempts of an adequate dose and duration of a minimum duration of 4 weeks." This is the evidence-based definition from the publication "Definition of Treatment-Resistant Depression in the Medicare Population" produced by the Agency for Healthcare Research and Quality (AHRQ) through its Evidence-based Practice Centers (EPCs) in response to the request of Centers for Medicare & Medicaid Services (CMS). [21]

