## **5.7 Masking/Blinding of Study**

The proposed study is an open-label feasibility trial and does not have subject blinding procedures. However, study personnel performing tDCS treatments will not perform the clinical assessments/ratings on outcome measures, and vice versa.

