### **Secondary Hypothesis:**

**Hypothesis 2.2.1.a:** We hypothesize that patients treated with the 5-day tDCS treatment protocol will have a decrease in mean MADRS scores post-tDCS.

**Hypothesis 2.2.1.b:** We hypothesize that patients treated with the 5-day tDCS treatment protocol will demonstrate changes in cognitive measures (Stroop Test, HVLT-R, and DSCT) post-tDCS.

T-tests or Wilcoxon signed rank tests will be used to compare pre- and post-tDCS measures on depression rating scales (MADRS, SHAPS) and cognition (Stroop, HVLT-R, DSCT). The effect sizes reported will include the proportion that improved, and both raw mean and standardized mean differences, i.e., Cohen's d.

**Hypotheses 2.2.2.a:** We hypothesize that the baseline PAF will have an indirect correlation with baseline MADRS scores in depressed patients.

**Hypothesis 2.2.2.b:** We hypothesize that there will be an increase in mean PAF scores after the 5-day tDCS treatment protocol.

Pearson or Spearman correlation will be used to estimate the correlation between MADRS scores and PAF at baseline. T-tests or Wilcoxon signed rank tests will be used to compare pre- and post-tDCS PAF scores. The effect sizes reported will include the correlation coefficient, proportion that improved, and both raw mean and standardized mean differences, i.e., Cohen's d. Treatment response will be defined as 50% or more improvement in MADRS score at post-treatment from pre-treatment. In the context of exploratory analysis, logistic regression will be used to assess associations between treatment response with each baseline characteristic.

**Hypothesis 2.2.2c:** We hypothesize that baseline characteristics (*ACE, pIQ, WRART, SES*) *will be predictive of treatment response.*

Pearson or Spearman correlation will be used to estimate the correlation between MADRS scores and PAF at baseline. T-tests or Wilcoxon signed rank tests will be used to compare pre- and post-treatment PAF scores. Treatment response will be defined as 50% or more improvement in MADRS score at post-treatment from pre-treatment. Logistic regression will be used to assess associations between treatment response with each baseline characteristic.

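### The prescribed EEG file name shows whether a recording is pre or post, and the protocol provides no recoding or masked processing before peak alpha frequency is derived

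*Protocol*

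**What the plan says.** **File naming.** Protocol Section 5.3, under EEG recording, gives the operator a directive: "Enter the following for the filename", followed by the pattern "tDCS\_[subject number]\_[pre OR post"]. The time point is a required part of the name.

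**Hypothesis and test.** Section 2.2 states the direction in advance: "We hypothesize that there will be an increase in mean PAF scores post-tDCS". Section 7.2 gives the analysis: "T-tests or Wilcoxon signed rank tests will be used to compare pre- and post-tDCS PAF scores".

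**Standing of the endpoint.** Section 3.3 places PAF among the exploratory endpoints: "An exploratory marker of response to tDCS is EEG peak alpha frequency (PAF) which will be measured pre- and post-tDCS".

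**Masking.** Section 5.7 says "The proposed study is an open-label feasibility trial and does not have subject blinding procedures". The one safeguard it adds is that "study personnel performing tDCS treatments will not perform the clinical assessments/ratings on outcome measures, and vice versa".

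**How PAF is obtained.** Section 1.4.1 refers to "a CGX wireless EEG system that will be used to generate a peak alpha frequency (PAF"). Sections 1.1 and 3.1 describe PAF as the frequency of greatest power, or the greatest magnitude, within the alpha band. The protocol does not say who processes the recordings, by what steps, or from which channels.

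**The concern.** This is a single-arm, open-label study, so most of its outcomes cannot be protected from expectation. PAF is one that can be protected to a useful degree. It comes from a saved recording, and whoever processes that recording need not know when it was made. The protocol does not use this opportunity. It prescribes a label that discloses the time point and says nothing about removing the label before processing.

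This matters because the hypothesis has a direction. If segments or channels are rejected by judgement, a person who can see 'post' on the file may, without intending to, make choices that favour a higher value. There is no comparator in which the same tendency would show up. An avoidable source of bias would then be mixed into a change that the study wants to read as a possible sign of target engagement.

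**Working it through.** No arithmetic applies to the main point, because the protocol gives no PAF variability, effect size or power figure. The check is whether any section breaks the link between the label and the person deriving PAF.

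1. **Is the label mandatory?** Yes. Section 5.3 words it as an instruction, with the time point as a fixed element.
2. **Is the tested hypothesis directional and uncontrolled?** Yes. Hypothesis 2.2.2b predicts an increase, Section 7.2 compares pre with post, and Section 5.2 confirms that all subjects receive the same treatment.
3. **Does Section 5.7 mask EEG processing?** No. It separates those who treat from those who assess or rate. A person who never delivers treatment can still read the time point in a file name.
4. **Does the identification code in Section 10.1 (item 3, Subject Privacy) mask the time point?** No. It replaces the subject's identity for privacy. The file name uses the subject number and then adds the time point.
5. **Would files go to an outside reader who might recode them?** Nothing suggests so. Section 10.1 (item 6) makes the investigator and study team responsible for collection, management and processing, and item 4 rules out external data sharing. Processing is therefore in-house, by the team that collects files under their prescribed names.
6. **Is there any room for discretion?** Possibly. Section 6 gives 15-20 minutes of recording, and Section 5.1 describes dry sensors in a 10-20 layout. Objective 2.2.2 refers to the stimulated region without naming channels. Choices of segment and channel are therefore open in this document. The choice between two peaks is less open, since Sections 1.1 and 3.1 point to the strongest one.

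**Workload of a remedy.** Section 7.1 gives a target of 10 subjects, and the Section 6 schedule gives one EEG before and one after treatment: 10 x 2 = 20 files. Replacing withdrawn subjects (Section 4.4.1) could add a few.

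**The case against.** The strongest reply is that the file name is an acquisition label. The operator necessarily knows the time point, and the label keeps each subject's two files from being confused. Files can be copied under codes later. A reader might infer that the naming rule makes masked reading impossible, or that the person deriving PAF is certain to know the time point. The documents do not support either inference: the rule does not prevent recoding, and the protocol names no reader and describes no manual cleaning step.

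A second reply is that artefact rejection and PAF extraction belong in a statistical analysis plan or an EEG manual that is not shown here. That is fair for the processing detail, and its absence is not the point. The naming rule, however, is something this protocol does fix, and nothing in it points to a later step that undoes the disclosure.

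A third reply is that PAF is defined by maximum power and may be generated by software, which would leave little to judgement. This stands in part. It removes most of the worry about picking peaks by eye and would make any bias small if the whole derivation is automated. The protocol does not commit to automation, so segment and channel choices remain.

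A fourth reply is that the missing control arm, and the medication changes allowed under Section 5.5, limit the PAF comparison more than any label does. That is correct. Recoding would not cure those limits; it would remove one further source of bias that is avoidable.

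**Conclusion.** The point holds in a limited form. The protocol prescribes a file name that discloses the time point and provides for neither recoding nor masked processing before PAF is derived for a directional, uncontrolled hypothesis. Followed as written, it leaves the time point visible during any discretionary step.

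The size of any bias cannot be quantified. A reader might be tempted to assume a number of ambiguous recordings, a gap between peaks and a standard deviation of change, and to turn these into a standardised shift. None of those inputs is in the protocol, and its definition of PAF already argues against free choice between peaks, so no such figure is offered here.

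A reader might also extend the point to the fNIRS recordings. The documents do not support that: Section 5.3 sets no time-point naming rule for NIRSIT files, and it describes channels passing calibration against a signal-to-noise reference value.

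The consequence is confined to an exploratory marker in a 10-subject pilot. The primary endpoints of feasibility, acceptability and tolerability are untouched. This is a low-severity, low-cost improvement. It assumes that no unseen document already provides for coded processing.

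**What to change.** In Section 5.3 (EEG recording), do one of the following:

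- replace the file-name rule with a random recording code; or
- keep the acquisition label and add that files are copied under random codes before artefact rejection and PAF extraction.

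In Section 5.7, state that EEG processing is done on the coded files, and that a study team member who does not process the EEG holds the key until PAF values are locked.

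The cost is about a sentence in each section and a link list for about 20 files. There is no new patient procedure or burden. The small downside is that the list must be kept without error, since a mistake would swap or misassign recordings. One team member must also be kept out of EEG processing to hold the key. The change should be made before any recording is processed, because masking cannot be restored once files have been read with their labels.
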